## Abstract

Breast milk from people with overweight/obesity may differ in composition compared with that from normal-weight people. Exercise training can modify breast milk composition in rodent models, with a beneficial impact demonstrated on the offspring’s metabolism, but whether these findings translate to humans is unclear. This trial aims to determine the effect of an exercise intervention on breast milk composition and whether an exercise-induced modification of breast milk impacts the infants’ growth and body composition. Effect of Exercise Training on Breastmilk Composition is a randomised, controlled trial with two parallel groups, one exercise group and one control group, with a 1:1 allocation. We will include a minimum of 62 exclusively breastfeeding participants, 6 weeks postpartum. The exercise intervention lasts 8 weeks and comprises 25 supervised endurance exercise sessions with moderate or high intensity. The primary outcome measure is the change in the relative concentration of the human milk oligosaccharide 3′sialyllactose in breast milk from baseline at 6 weeks postpartum to the end of the intervention period. Secondary outcomes include breast milk concentrations of other metabolites, cytokines, hormones and microRNA, maternal health outcomes, infant growth, infant gut microbiome and infant circulating microRNA. Maternal and infant outcomes will be measured before, during and after the intervention period, with a follow-up of the infants until they are 24 months old. Trial registration number NCT05488964.

WHAT IS ALREADY KNOWN ON THIS TOPICWHAT THIS STUDY ADDSThis is the first randomised controlled trial to determine the effect of endurance exercise training on a comprehensive range of breast milk components.HOW THIS STUDY MIGHT AFFECT RESEARCH, PRACTICE OR POLICYThis study may provide scientific knowledge to guide the development of specific exercise recommendations for postpartum individuals with overweight/obesity.This study could be informative for improving infant formula by increasing knowledge of exercise’s beneficial or detrimental effects on human breast milk composition.

## Introduction

 Between 1980 and 2015, global obesity rates doubled in children aged 2–4 years and increased eightfold among 5–19 year olds.^1^ Up to 21% of the population attributable risk for childhood obesity is accounted for by maternal obesity,^2^ which implies a strong mother-to-child transmission. This transmission of obesity risk is not solely genetic. It also involves interactions between genes and an ‘obesogenic’ environment modifying gene expression (epigenetic modifications) and phenotype.^3^ During the ‘first 1000 days’ of life (from conception to the age of 2 years), humans are particularly sensitive to epigenetic modifications that may lead to childhood obesity: nutrition in this period greatly impacts later susceptibility to obesity.^4^ Breastfeeding is one factor that may be important for preventing childhood obesity, as observational data show that breastfed children have a 13% lower likelihood of becoming overweight or obese compared with formula-fed children.^5^ As such, the WHO recommends exclusive breast feeding until infants are 6 months of age to protect against obesity.^6^ However, there is evidence that breast milk composition is associated with the mother’s metabolic health.^7^,^13^

Some breast milk components, such as human milk oligosaccharides (HMOs), are associated with infant obesity, with different concentrations also observed between normal-weight lactating people and those with overweight (body mass index (BMI) 25.0–29.9 kg/m^2^) or obesity (BMI>30 kg/m^2^).^10^ Maternal obesity is further associated with other differences in the breast milk metabolome.^7 8^ Both maternal BMI and infant adiposity are associated with increased breast milk levels of the metabolites 5-methylthioadenosine, mannose, lyxitol and shikimic acid.^7 8^ The levels of breast milk components considered non-nutritive, including microRNA (miRNA) and hormones, have also been associated with maternal BMI. Breast milk is rich in miRNAs, potentially acting as epigenetic regulators.^14^ The associations between selected miRNAs in breast milk and maternal BMI have been reported, and the studies included a suggestive link to infant body composition.^11 12^ However, these two studies examined two different sets of selected miRNAs, and the evidence concerning the effect of breast milk miRNAs on infant body composition remains uncertain.

The possible role of certain breast milk components in the mother-to-child transmission of obesity is supported by several studies in mice. For instance, offspring born to lean dams and cross-fostered by obese dams displayed a dysmetabolic phenotype.^15^ In addition to maternal BMI, maternal diet, smoking, mode of delivery and gestational diabetes may affect breast milk composition.^13 16 17^ Maternal physical exercise, however, has received very little attention with respect to breast milk composition. Exercise is a substantial regulator of overall systemic metabolism and affects multiple cells, tissues and organs through the increased metabolic activity of contracting skeletal muscles. The exercise-induced health benefits stem from integrating intertissue communication through signalling molecules, hormones and cytokines collectively termed ‘exerkines’.^18^ Whether these whole-body effects of exercise also affect breast milk composition is unknown.

There is currently sparse research on the effect of exercise on human breast milk. The existing evidence comes from research undertaken before the technological advent, which now allows for detailed analyses of breast milk composition. Evidence for a protective role of ‘exercised’ breast milk on offspring obesity risk is, so far, only seen in mice.^19^ Maternal exercise was shown to increase the abundance of the HMO 3′sialyllactose (3′SL) in mouse milk, which was crucial for mediating improvements to metabolic health in the offspring.^19^ It is not known whether these findings translate to humans. Consequently, we designed a randomised controlled trial (RCT) to determine the effect of exercise during lactation on breast milk composition in people with overweight/obesity.

### Aims and hypotheses

The primary aim of the Effect of Exercise Training on Breastmilk Composition (MILKSHAKE) trial is to determine the effect of exercise during lactation on relative concentrations of 3′SL in breast milk in people with overweight/obesity. The secondary aims are to investigate if maternal exercise during lactation affects other breast milk components, maternal health outcomes, infants’ weight gain and body composition and to investigate potential mechanisms explaining the effect of exercised breast milk on infant obesity risk. Our primary hypothesis is that 8 weeks of exercise training starting 6 weeks postpartum will increase the relative concentration of 3′SL in breast milk.

## Methods

### Design and study setting

The MILKSHAKE trial is an RCT with two parallel groups: an intervention group (exercise training) and a standard care control group (figure 1). We will obtain data and biological material from the participants and/or their infants at baseline before randomisation (6 weeks after delivery), after 4 weeks (10 weeks after delivery), after 8 weeks (14 weeks after delivery) and when the infants are 26 weeks, 40 weeks, 12 months and 24 months. We will additionally collect growth data from local health centres. The trial is undertaken at the Norwegian University of Science and Technology (NTNU) in Trondheim, Norway, in collaboration with the St. Olav’s Hospital and Trondheim municipality. We used the Standard Protocol Items: Recommendations for Interventional Trials reporting guidelines to report the trial protocol.^20^

**Figure 1 F1:**
[figure not shown]
Study design. Overview of the design of the Effect of Exercise Training on Breastmilk Composition randomised controlled trial.

### Recruitment and participants

Participants will be recruited by invitations to those who have delivered a baby at the St. Olav’s Hospital maternity ward, through posts in local health centres, and via announcements on hospital and university webpages, local stores and social media. Box 1 shows the inclusion and exclusion criteria for participation.

Box 1Inclusion and exclusion criteriaInclusion criteriaAge ≥ 18 years.Given birth to a singleton term baby (after 37 weeks +0 days).Prepregnancy body mass index (BMI) ≥ 25 kg/m^2^ and/or postpartum BMI ≥ 28 kg/m^2^ 1 week or more after delivery.Exclusively breast feeding the baby (no other foods are given) and intend to continue this practice for ≥ 8 weeks at inclusion.Understands oral and written Norwegian language.Able to attend supervised exercise sessions at the St. Olav’s Hospital.Exclusion criteriaOngoing pregnancy.Known diabetes (type 1 or 2).Known cardiovascular diseases.High-intensity endurance exercise ≥ 2 times per week in the last 3 months and/or an intention to start regular endurance exercise within the next 8 weeks at baseline.

### Randomisation and allocation

Following screening and initial assessments, participants will be randomly allocated (1:1) after stratifying for gestational diabetes (yes/no) to the intervention or control groups. We will use a computer random number generator developed and administered at the Clinical Research Unit (Klinforsk), St. Olav’s Hospital, to randomly allocate participants. The allocation of participants is concealed until a participant is included. Block randomisation minimises any imbalance in group allocation, and the block sizes vary with the size of the blocks unknown to the researchers to maintain allocation concealment.

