#### Univariate analyses

We plan to use LMMs for between-group comparisons of the maternal outcomes described and for the comparison of infant anthropometrics and body composition. Each model will include time and group×time interactions as fixed effect variables and subject (participant ID) as a random factor.^28^ In these analyses, we will consider the baseline values equal in both groups as there are no expected systematic differences between groups in RCTs. We will report estimates with 95% CIs and p values for group differences. In the case of non-normal model residuals, we will perform bootstrapping, transformations or non-parametric methods.

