#### Sensitivity analyses

In the analyses of breast milk data, we will do additional analyses adjusted for the participant’s secretor status, which reflects their blood group antigens and is an important determinant of HMO abundance in breast milk. The secretor status of each participant will be determined by the high abundance (secretor) or near absence (non-secretor) of the HMO 2′fucosyllactose in the milk samples.^16^ We will also perform per-protocol analyses, in which we include only the participants in the intervention group who completed ≥ 20 exercise sessions (adherence ≥ 80%).

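### Randomisation is stratified by gestational diabetes, but the one mixed model with listed terms omits it and no other described analysis mentions it

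*Protocol article*

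**What the plan says.** Randomisation and allocation: "participants will be randomly allocated (1:1) after stratifying for gestational diabetes (yes/no) to the intervention or control groups". Allocation is blocked: "Block randomisation minimises any imbalance in group allocation, and the block sizes vary". Gestational diabetes is the only stratification factor named.

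Introduction: besides maternal BMI, "maternal diet, smoking, mode of delivery and gestational diabetes may affect breast milk composition".

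Univariate analyses: "We plan to use LMMs for between-group comparisons of the maternal outcomes described and for the comparison of infant anthropometrics and body composition". The terms are then listed: "Each model will include time and group×time interactions as fixed effect variables and subject (participant ID) as a random factor". Baseline is constrained: "we will consider the baseline values equal in both groups".

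Multivariate analyses names methods for the omics, cytokine, microRNA and microbiome data but lists no covariates. No model is named for 3′SL, the primary outcome, which is defined as a change from baseline to 8 weeks.

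Sensitivity analyses adds a per-protocol set and an adjustment of the milk data for secretor status, which "is an important determinant of HMO abundance in breast milk". Gestational diabetes does not appear there.

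**The concern.** Blocked randomisation within strata removes most of the chance imbalance in gestational diabetes between the arms. The true sampling variance of the group difference falls accordingly. A model without the factor still counts the variation between strata as residual error, so its standard error describes a design with more chance imbalance than this one has. Confidence intervals are then too wide, true type I error falls below the nominal 5%, and some power is lost.

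This goes further than a detail left for later. For the maternal and infant outcomes the article gives a list of model terms, and for the milk outcomes it specifies an adjusted analysis. The one factor built into the allocation appears in neither. The mixed-model outcomes include fasting glucose, insulin/C-peptide and glycated haemoglobin, for which gestational diabetes is an obvious candidate predictor.

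At stake is efficiency, and agreement between analysis and design, in a trial of about 52 completers. Validity is not in question.

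**Working it through.** **The plan's own figure.** The documents give no figure for the effect of the stratum. The one relevant calculation is the sample size: difference 2900 − 2500 = 400, SD 200, so d = 2.0. The normal approximation gives n = 2 × (1.960 + 1.282)² / 2.0² = 5.25, so 6 per group, with 88.5% power at 5. That is close to the stated five at 90%. The exact t-test gives 79.0% at 5 per group and needs 7 for 90%. The total of 62 is a judgement and does not follow from these inputs. It leaves 62 × 0.85 = 52.7, about 52 completers or 26 per arm, where d = 0.79 is detectable with 80% power.

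**Inputs not in the documents (assumed).** Prevalence p of gestational diabetes 0.1 to 0.3; its effect 0.5 or 1 SD; correlation between baseline and follow-up 0.6.

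**Formula.** If a perfectly balanced binary stratum with effect g (in residual SDs) is omitted, the model's standard error is too large by √(1 + p(1−p)g²). True two-sided type I error is about 2[1 − Φ(1.96 × that factor)].

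| p | g | SE factor | approx. type I error |
|---|---|---|---|
| 0.1 | 0.25 | 1.003 | 4.9% |
| 0.1 | 0.5 | 1.011 | 4.8% |
| 0.3 | 0.5 | 1.026 | 4.4% |
| 0.1 | 1.0 | 1.044 | 4.1% |
| 0.3 | 1.0 | 1.100 | 3.1% |

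The factor cannot be below 1, so the error is always on the conservative side.

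**Simulation.** N = 52, blocks of 4 or 6 within stratum, 5000 runs per cell. The model is a regression of the follow-up value on group and baseline, with or without gestational diabetes; it stands in for the mixed model with baseline constrained equal. The treatment effect is 0.65 SD. An SD here is that of the outcome at one visit within a stratum. *Stable* means the same effect of gestational diabetes at both visits; *change* means an effect at follow-up only.

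| p | effect | type I error without → with | power without → with | gain (points) |
|---|---|---|---|---|
| 0.1 | stable 0.5 | 5.4 → 5.5% | 81.5 → 81.3% | −0.2 |
| 0.3 | stable 0.5 | 5.0 → 5.1% | 80.2 → 80.2% | 0.0 |
| 0.1 | stable 1 | 5.1 → 5.1% | 81.1 → 81.4% | 0.3 |
| 0.3 | stable 1 | 4.9 → 5.2% | 80.1 → 81.5% | 1.4 |
| 0.1 | change 0.5 | 4.5 → 5.1% | 79.5 → 80.1% | 0.7 |
| 0.3 | change 0.5 | 4.2 → 5.0% | 78.5 → 80.5% | 2.0 |
| 0.1 | change 1 | 4.1 → 5.3% | 76.0 → 80.0% | 4.0 |
| 0.3 | change 1 | 2.8 → 5.2% | 71.3 → 80.6% | 9.3 |

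The Monte Carlo standard error is √(0.05 × 0.95 / 5000) = 0.3 points for type I error and √(0.8 × 0.2 / 5000) = 0.6 points for power.

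**Agreement of the two.** With correlation 0.6 the residual SD given baseline is √(1 − 0.36) = 0.8. A 1 SD change is therefore g = 1/0.8 = 1.25 residual SDs. At p = 0.3 the factor is √(1 + 0.21 × 1.5625) = 1.152, an approximate type I error of 2.4%. The simulated 2.8% is slightly higher, as incomplete blocks leave the balance short of perfect.

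**Secretor status.** With an assumed 1 SD stable effect in 20% of participants, type I error stays near 5% with or without the term, and adding it changes power by about 1 point or less once baseline is modelled. For example, at p = 0.3 with a stable 0.5 SD effect of gestational diabetes, power is 79.2% without secretor status and 79.9% with it.

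**The case against.** The strongest reply is that the omission is shown only where it may matter least. The listed terms belong to the model for maternal and infant outcomes, while the Introduction's remark concerns milk and says only that gestational diabetes may affect it. Baseline handling already absorbs most of a stable difference between strata. A full covariate list is also something an article may leave to an analysis plan. Most of this stands, and it limits the point. What remains is that the article does list the terms of one model and does not include the factor used in the allocation.

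Three stronger readings are tempting, and the documents do not support them.

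- A reader might infer that every model, including the primary one, omits the factor. No model is named for 3′SL, and the multivariate methods carry no covariate list. What can be said is that no described analysis includes it.
- A reader might infer that the p values are unreliable in a way that threatens the conclusions. Any departure is conservative: false positives are not inflated and the estimate is not biased.
- A reader might infer that keeping secretor status to a sensitivity analysis is the same fault. Randomisation is not stratified on it, so leaving it out does not miscalibrate the test. The adjusted analysis is already prespecified, and a change or baseline-constrained analysis absorbs most of a stable effect. The plan's choice is defensible.

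**Conclusion.** The point holds as a modest matter of efficiency and consistency. The trial stratifies on gestational diabetes, the mixed model's listed terms leave it out, and no other described analysis mentions it. Under an assumed prevalence of 10–30%, 52 completers and a baseline correlation of 0.6, the loss is about 0–2 power points for a stable effect or a 0.5 SD effect on the change. It reaches about 4–9 points, with type I error of about 3–4%, only if gestational diabetes shifts the change by a full SD, which is an extreme case. None of these inputs can be taken from the documents, so the true loss is unknown within that range. The direction is certain: standard errors too large, never too small.

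**What to change.** In Univariate analyses, add gestational diabetes (yes/no) and its interaction with time as fixed effects in the mixed models. State that the primary between-group comparison of 3′SL uses the same adjustment. The interaction is needed because an effect on the change, which baseline does not absorb, is where the loss arises.

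The cost is a sentence and a few degrees of freedom. With time as a categorical variable, the three maternal visits (baseline, 14 and 40 weeks) need 1 + 2 = 3 extra parameters, and the four laboratory visits for infants need 1 + 3 = 4. A single-visit baseline-adjusted comparison of 3′SL needs 1. The simulation tested only this last form and found no material power loss from adding the term when it was not needed. Health-centre growth data, with more ages, would need more parameters if time is categorical.

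The article reports 21 participants included and recruitment still open, so at that date the term could be fixed before outcome data were analysed. The secretor-adjusted analysis needs no change.

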### Intervention

The exercise intervention consists of supervised endurance training, starting 6 weeks after delivery and continuing for 8 weeks. The participants will walk or run on treadmills, progressively increasing exercise volume and intensity. In the first week, they will complete two moderate-intensity sessions, lasting 40 and 45 min, respectively. After that, they will exercise three times per week for most of the remaining weeks, with four sessions in the 6th and 7th weeks (table 1). If participants miss a session in one week, they can add this session to the following week.

**Table 1 T1:** Overview of exercise intervention

Week	Session 1	Session 2	Session 3	Session 4
1	40 min MOD	45 min MOD		
2	40 min HIIT	50 min MOD	45 min HIIT	
3	45 min HIIT	60 min MOD	45 min HIIT	
4	50 min HIIT	40 min HIIT	45 min HIIT	
5	60 min MOD	50 min HIIT	45 min HIIT	
6	60 min MOD	45 min HIIT	30 min HIIT	40 min HIIT
7	40 min HIIT	50 min MOD	50 min HIIT	60 min MOD
8	45 min HIIT	40 min HIIT	40 min HIIT	

Sessions with moderate intensity (MOD) will be continuous walking/running, and sessions with high intensity (HIIT) will be walking/running with repeated high-intensity work bouts.

The exercise intensity during the moderate-intensity sessions will be 70%–75% of the individual heart rate maximum, whereas the aim is to reach 90%–95% of the heart rate maximum during the high-intensity interval sessions. We will monitor exercise intensity by heart rate monitors (Polar, Finland). Participants needing to use ergometers other than a treadmill due to bodily pain can exercise on a stationary bike or an elliptical trainer. Participants in the control group will receive standard care and be asked to continue their habitual physical activity level. They will not be discouraged from being physically active. Neither group will receive any dietary advice.

### Experimental procedures and outcome measures

The study period spans from baseline assessments and up to the infants are 24 months old (figure 2). The participants visit the lab for assessments at baseline (6 weeks postpartum), mid-way through the intervention period (10 weeks postpartum), after the end of the 8-week intervention period (14 weeks postpartum) and after 40 weeks from delivery. We will collect data on infant growth from local health centres until the infants are 24 months old.

**Figure 2 F2:**
[figure not shown]
Overview of study visits schedule and procedures.

#### Breast milk sampling

Breast milk will be sampled at three time points: at baseline (6 weeks postpartum), after 4 weeks (10 weeks postpartum) and after 8 weeks (14 weeks postpartum). The participants will receive an electric breast pump (Medela, Switzerland). They will be given a detailed instruction sheet and a link to a video for standardised milk collection procedures. The participants will fully express from one breast to minimise differences due to hindmilk versus foremilk variations. The full sample will be gently mixed, and 40 mL will be taken for our research, with any remaining milk being left for the participants’ use. To minimise diurnal variations, the participants will express milk at the second feeding of the day (or before 09:00). They will fast for >2 hours before collection. Data collection, including breast milk and blood sampling, will be undertaken 36–48 hours after an exercise session to optimise the capture of chronic adaptations to exercise. The participants will store the breast milk in their home refrigerator until they deliver it to the laboratory the same day, transported in a container with cooling elements. Samples will be aliquoted into sterile cryotubes and frozen at −80°C until analysis. We will separate some fresh breast milk into fat, whey (skimmed) and cells by centrifugation, whereas the remaining milk will be frozen as full milk.

#### Primary outcome measure

The primary outcome measure is change in the relative concentrations of breast milk 3′SL from baseline to after 8 weeks (14 weeks postpartum). We plan to do untargeted metabolomics using ultra-high-performance liquid chromatography tandem mass spectrometry (UPLC-MS/MS; positive mode), UPLC-MS/MS (negative mode) and gas chromatography-MS at Metabolon (USA).

